### Study settings

The laboratory tests and interventions are performed and managed at the Department of Sport Medicine, Shanghai University of Sport, the Yangpu District Health Care Service Centres and the Department of Endocrinology, Shidong Hospital, and Clinical Nutrition Centre at Fudan University Huadong Hospital, Shanghai, China.

### Interventions

1. Exercise group:

Specific supervised individualized exercise (mainly aerobic exercise such as Nordic brisk walking + stretching and other group exercise) programs will be developed by an exercise researcher after baseline assessments on the basis of each individual’s fitness level. The supervised exercise program will be progressive and variable and will be monitored by an exercise researcher during the course of the study. The intensity and duration of exercise will be increased from 60% to 75% of the maximum oxygen uptake (estimated from fitness test) and from 30 to 60 min per session, and the frequency from 3 to 5 times a week, and will be updated monthly.

2. Diet group:

Dietary programmes are developed after baseline assessments on the basis of each individual’s current dietary intakes and body weight. Overweight/obese participants are advised to moderately reduce their total energy intake (by 300–500 kcal per day for the first 3 months) with guidance on the proportion of macronutrients to be consumed. The target is to reduce body weight by 3 kg in the first 3 months of the intervention. After this period, the participants are advised to maintain their achieved body weight reduction, and continue to gradually reduce their body weight towards normal levels, with a target of a 10% reduction from their initial body weight. Participants with normal weight are advised to maintain their body weight.

During the intervention, each meal is planned by a clinical nutritionist. We provide lunch daily to each participant during the course of the intervention. The lunch accounts for 40% of the total daily energy intake. The breakfast and dinner each account for 30% of the total daily energy intake. The proportion of macronutrients are planned as 30-40% carbohydrate with < 5% sucrose and with 18-20% as fiber, 40% fat (SAFA 10%, MUFA 15-20%, PUFA 10%) and 20% protein. The lunch will be prepared under the guidance of a clinical nutritionist at the Student Restaurant of Shanghai University of Sport. Each meal will contain three to four dishes of foods commonly eaten by Chinese families in Shanghai. A trained study staff member will weigh each item for each specific person according to the dietary plan and the cooked dishes will be put into a named lunch box for each participant. The lunch box will be then delivered to the study district office where the study subjects are gathered and the eating will be monitored. If the participants don’t have time to come to the lunch, the lunch box will be delivered to their home and we will ask the participants to take it as their dinner.

The subjects will cook their breakfast and dinner by themselves and eat the proportion following the nutritionist advices. They will take the pictures of each meal by an iPhone provided by the research. A researcher will upload the pictures weekly to our data management server for further evaluation.

3. Exercise + diet group:

The AEx + LCh group will perform the same exercise program and follow the same diet program as abovementioned for AEx and LCh groups.

4. Control and reference groups:

The control and reference groups will be advised to maintain their level of physical activity and habitual eating during the intervention. After intervention, we will provide to the control group an opportunity to participate in our planned exercise and diet intervention for 3 months.

### Primary and secondary outcomes

#### Primary outcomes

1. Liver fat content

2. Serum metabolomics, level of glucose, insulin, triglycerides and free fatty acids

3. Gut microbiota composition

The measurements of liver fat content, variables related to glucose metabolism, triglycerides and free fatty acids will be assessed at baseline and 6-month follow-up; gut microbiota composition will be measured at baseline, 3-month and 6-month time points.

### Secondary outcomes

1. Questionnaires of behavioural characteristics, diet, physical activity, health condition and medications

2. Anthropometry (height, body weight, body size demission of different region of body)

3. Blood pressure

4. Body composition (fat mass, lean mass and bone mass)

5. Physical fitness and heart rate (2 km walk and 3 minutes step tests)

6. Muscle strength (maximal isometric voluntary contraction of the right grip, left elbow flexors and left knee extensors)

7. Venous blood sample (total cholesterol, HDL-cholesterol, LDL-cholesterol, apolipoproteins A-I and B, lipoprotein(a), cholesterylester fatty acid composition, hormones, cytokines and serum metabonomics)

The secondary outcome measures will be assessed at baseline, 3- and 6-month time points except for body composition (fat mass, lean mass and bone mass) and blood sample which will be performed at the baseline and 6-month time points.

### Measurements procedures

1. Screening:

The purpose of the screening is to verify the eligibility of potential participants. The recruitment of participants will be done at Yangpu District Health Care Service Centres and the Department of Endocrinology, Shanghai Shidong Hospital Shanghai, China. The potential subjects will be selected from the outpatient pool of those who have records of ultrasound for evaluation of liver fat and fasting blood results for diagnosing diabetes from 2012 to 2013. Registered nurses from health care centers will first contact the potential subjects and invite them to a study information meeting. Detailed information of the objectives of the study, its nature and constraints, the anticipated risks and the expected benefits are given by the investigating physician of endocrinology and professor of sport medicine in the recruitment information meetings. When the screening consent form has been signed, patients will be asked to fill in a screening questionnaire to check their health and medication background as well as alcohol consumption, and to undergo a glucose tolerance test (blood draw after overnight fasting, followed by samples of 30 minutes and 2 hours after the intake of 75 g of glucose).

2. First visit of the Run-in Trial:

The run-in trial consists of an 8-week period during which the participants who are qualified in terms of the screening questionnaire will complete all of the forms and protocols required for successful entry to the 1-year study. The purpose of the run-in trial is to identify and exclude those individuals who cannot or will not fulfil the requirements of the study. This should decrease the dropout rate of the 1-year study. We anticipate that approximately 50% of potential participants will not complete the run-in trial with sufficient detail or completeness to be entered in the study.

In the first visit of the Run-in Trial, those subjects qualified by screening (subjects who have fasting glucose level between 5.6 and 6.9 mmol/L or after 2-h intake of glucose between 7.8 to 11.0 mmol/L are willing to participate in this study will be invited for further blood sample collection. In addition, the pre-diabetes and healthy reference groups will undergo the same procedure. During the first visit, the participants will receive an in-depth explanation of the 1-year study and informed consent for the intervention and follow-up study will be obtained in writing.

3. Second visit of Run-in Trial:

At the second visit, a physician and a researcher will examine all the results of the first visit to verify that the subject meets the inclusion criteria. If a person is qualified for participation in the study, he or she will be invited to the laboratory at the Department of Sport Medicine, Shanghai University of Sport for demographic, health history and physical activity questionnaires, height, weight, waist circumference, blood pressure, physical performance, body composition by DXA, as well as instructions for fecal sample and 24 hours urine collections. They will be also invited to have a magnetic resonance spectroscopy (^1^H MRS) scan to evaluate whether they have NAFLD (>5% liver fat content). The qualification of the participants will be established after this visit and randomization will be performed.

4. Randomization visit:

When the qualified subjects are randomized, an information meeting will be organized for each group. Detail of the activities during intervention will be explained by a principle investigator or a co-principle investigator. For the AEx group, we will provide walking poles and teach them how to use it. A heart rate monitor (M5 Suunto Oy, Finland) will be provided during each exercise session to monitory the intensity and duration of exercise. For the LCh group, a dietary consultation will be organized to instruct subjects how to prepare their breakfast and dinner and what we are going to provide them for lunch during the intervention. In addition, we will provide a mobile phone to each subject and teach them how to take pictures of their breakfast and dinner. For the AEx + LCh group, we will provide instructions as abovementioned both for exercise and diet groups. For the control group and both reference groups, we will emphasize the importance of their participation in study and instruct them to maintain their habits during the intervention. All groups will be instructed to fill a daily diary regarding their daily activities and a step counter will be provided to them to monitory their daily walking status.

5. Follow-up visits:

The purpose of the follow-up visits is to monitor the compliance, enhance retention of the subject in the study, and obtain information on factors that may affect outcomes of the study. After the randomization visit, a study coordinator will contact participants every month to check their exercise records and update the exercise program. The study coordinator will also give feedback of their dietary intake on the basis of the images of meals and snacks provided by the subjects themselves. The participants will have follow-up visits to the laboratory of Shanghai Sport University at months 3, 6, 12. Their height, weight, food frequency questionnaire, physical activity record, fitness tests, blood pressure, blood samples, fecal samples, urine samples and changes in health status will be checked at those time points. MRI and DXA will be included in the follow-up visits for months 6 and 12.

### Methods of measurements

#### Questionnaire, anthropometry and physical examinations

Background information regarding lifestyle, behavioural and motivational characteristics as well as medical history will be collected by questionnaires. Data gathered from eligible subjects will then be used to describe the study populations, and individual results will be used to screen the changes and for monthly feedback.

Daily physical activity will be recorded through an activity diary (designed by the study) during the 6-month intervention and 6-month after intervention. In addition, food records will be collected 12 times to estimate the subject’s energy intakes and intake of different nutrients during the study for all groups. The collected information will be evaluated by exercise and nutrition experts, and feedback will be given by each individual’s family doctor.

Height will be determined using a wall-fixed measuring device, and weight using a calibrated scale. Height and weight will also be used to determine body mass index (BMI, weight(kg)/(height(m))^2^. Blood pressure will be measured after 5 min rest. A physician will examine the physical conditions of subjects and ensure that subjects meet the inclusion criteria.

#### Blood samples

Glucose tolerance tests will be performed after overnight fasting, 30 minutes and 2 hours after the intake of 75 g glucose for the assessment of serum insulin (chemiluminesent immunoassay) and glucose (automatic biochemistry analyzer).

Venous blood samples will be taken in standardized fasting conditions at 7–8 a.m. Total cholesterol, high-density lipoprotein (HDL), low-density lipoprotein (LDL), triglycerides, apolipoproteins A-I and B, lipoprotein (a), glucose, insulin, cholesterylester fatty acid composition, free fatty acid profile and sex hormones will be measured from serum sample by conventional methods. We will use appropriate methods to measure a range of factors related to inflammation. ELISA or Western Blotting can be used to assess serum samples for leptin, adiponectin, resistin, tumor necrosis factor alpha (TNFα), C-reactive protein (CRP), interleukin (IL-6), interleukin 1β (IL-1β), interleukin-1 receptor antagonist (IL-1Ra), and angiotensinogen, the fibroblast growth factor 23 (FGF23), Zn-metalloendopeptidase (PHEX), matrix extracellular phosphoglycoprotein (MEPE), and cartilage oligomeric matrix protein (COMP). Plasma samples will be used to assess lipopolysaccharides (LPS) concentration by Endosafe-MCS (Charles River laboratories, Lyon, France) based on the Limulus amaebocyte Lysate (LAL) kinetic chromogenic methodology that measures color intensity directly related to the endotoxin concentration in a sample.

Serum free fatty acid profile measurement will be performed in order to define the different fractions and ratio of saturated, mono-unsaturated and polyunsaturated fatty acids. The obtained information is needed to estimate certain de novo lipogenic enzymes activity by comparing the ratio of different precursors and end-products fatty acid metabolism in the serum. The information is also needed to evaluate how diet, physical exercise and liver fat affect the concentrations of free fatty acids and their ratios in the serum. Gas chromatography-mass spectrometer will be used for the analysis.

#### Fecal samples collection

The fecal samples (two samples per each time) will be collected during the second day of the 3-day dietary records collection. Detailed sample collection and transportation instructions are given by a study nurse. The study will provide to subjects the materials for sample collection and transportation from home to health care centre which including: 1 cool box, 2 plastic specimen jars (the cover of the jar contains the spatula), plastic bag, 4 cold chargers and plastic gloves. The subjects are advised to sample approximately 2–3 grams of feces by spatula attached to the cover of the plastic specimen jar. Then put fecal samples into the specimen jar and close it. The jars are stored in a plastic bag with the cool box. After samples are collected, the subjects will immediately deliver the samples to the health care centre (mostly about 5–10 min walking distance). If the subjects are not able to deliver the sample by themselves, the will call our research line and a personal from research group will pick up the samples from subjects home within 30 min to 1 hour.

Fecal samples are frozen after collection, stored at −80°C, and the DNA will be extracted with a fully automated instrument using magnetic beads-based technology (Genoextract, Hain Lifescience GmbH, Germany). Whole-genome sequencing will be performed using Illumina Hiseq 2000 system. In addition, fecal bacteria composition will be analyzed with a method based on flow cytometry, 16S rRNA hybridization, and DNA-staining. Different bacterial indices will be calculated to evaluate the inter-relationship of different bacterial species and how they are associated with liver fat content [8]. Concentrations of short chain fatty acids (SCFAs) will be determined in the supernatant using an Agilent 6890 N gas chromatograph with flame ionization detection and using ChemStation software for data processing.

#### Urine sample collection

Twenty-four hours urine samples will be collected in the morning after avoiding the first sample during the 2^nd^ to 3^rd^ day of the 3-days dietary records collection. The detailed instruction on urine sample collection will be given to the subject by a study nurse. Special sample collection device will be provided to the subjects. The device allows us to store small proportion of the total sample for whole day including information of total volume of samples. The sample will be stored at −80°C until analysis. The function of kidney and the concentration of minerals will be analysed.

#### Abdominal fat assessment

For abdominal fat assessment, axial T1-weighted dual-echo (in-phase and out-of-phase) Volumetric Interpolated Breath-hold Examination (VIBE) images will be obtained of the entire abdominal area with a single breath-hold using the following parameters: repetition time (TR) 4.36 ms, first echo time (TE1) 1.33 ms (out-of-phase) and second echo time (TE2) 2.45 ms (in-phase), slice thickness 4.8 mm, voxel size 1.9×1.3×4.8 mm, distance factor 20%, matrix 320 × 208, field of view (FoV) 40 cm, flip angle (FA) 9 degrees and average acquisition time of 15 s. Areas of abdominal subcutaneous, visceral and retroperitoneal fat will be semi-automatically segmented using the OsiriX software package (OsiriX Foundation, Geneva, Switzerland). Measured volumes of each of the abdominal adipose tissue compartments will be converted into tissue mass taking into account slice thickness and an adipose tissue density of 0.9196 g/ml [25].

#### Hepatic fat content assessment

Non-invasive measurement of hepatic fat content (HFC) will be performed using single-voxel proton magnetic resonance spectroscopy (^1^H MRS). The ^1^H MRS measurements will be performed on a 3 T Siemens Magnetom Verio scanner (Siemens Medical Solutions, Erlangen, Germany) using the appropriate elements of the Body Matrix and built-in spine coil as the receiving elements. A respiratory (bellows) gated point-resolved spectroscopy (PRESS) sequence with the following parameters will be used: TR 3000 ms, TE 30.0 ms, number of averages 24 (for both suppressed and unsuppressed water signals) and typical acquisition time of 1 min 24 s. Obtained spectra will be analysed using the Linear Combination of Model spectra software suite which is generally considered to be the gold standard for in-vivo spectroscopy analysis [26]. The fat and water spectrum signals will be corrected for differences in T2 decay, molar concentrations of ^1^H nuclei in fat and water and HFC will be defined as fat in relation to the total weigh of liver tissue, as previously described [23].

#### Body composition

Dual-energy X-ray absorptiometry (DXA Prodigy, GE Lunar Corp., Madison, WI USA with software version 13.60.033) will be used to estimate lean tissue mass (LM), fat mass (FM) and bone mass (BM) of the whole body, legs, arms, and trunk as well as android and gynoid regions. All metal items will be removed from the participants to ensure the accuracy of the measurement.

#### Fitness test and heart rate

2 km walking test will be performed by walking 2 kilometres as fast as possible on a flat surface [27]. The result is recorded as a fitness index taking into account person’s age, gender, height, weight, time taken to walk 2 kilometres and the heart rate at the end of the test. There are five fitness classes which can be used to compare result with the fitness of others of the same age and gender or a person’s own previous results and development between the tests. The individual’s result will be used to set up their own personalized exercise program.

The YMCA Step Test is a relatively low stress effort and therefore can be used for unfit individuals [28]. Beat-by-beat heart rate will be recorded continuously during 3 minutes exercise, and in a sitting posture at rest before exercise, and 1 minute after exercise [28].

#### Muscle strength test

Maximal isometric voluntary contraction (MVC) of the right hand grip strength, left elbow flexors and left leg extensors will be measured in a sitting position with an adjustable dynamometer chair (Good Strength). Subjects will be encouraged to exert their maximal effort during an isometric test for ~3 s. The MVC of the hand grip strength, elbow flexors will be measured with the subject’s forearm strapped at the wrist using Velcro straps with elbow at 90° and the thumb in an upward position. Seat height will be adjusted to ensure that the upper arm is at a 90° to the chest and the elbow is at the pivot point of the apparatus. In the measurement of MVC of knee extensors, the subject’s lower leg will be strapped at the distal end of the lower leg using Velcro straps with knee at 120°. Seat height will be adjusted to ensure that the hip will be at 90° to the trunk and the knee will be at the pivot point of the apparatus. The hip will be also strapped by Velcro straps to limit its movement.

#### Concomitant adherences and procedures

During the intervention, an exercise instructor will ensure that each individual has the right starting level and will follow their progress during the entire trial. We will organize the participants into groups according to their time and places of residence. Exercising together as a team will increase their compliance. A group leader of each 10 subjects will be selected by participants to assist the instructor to ensure a high participation rate. The exercise instructor will be with the subjects at least three times a week during the intervention. Group feedback meetings will be arranged every 3 months during the trial by an exercise specialist.

To ensure good compliance in diet intervention, we provide a mobile phone to the subjects to allow them to take photographs of their breakfast and dinner daily during the study. The photos are downloaded by a researcher weekly. The study nutritionist analyses dietary composition from the uploaded photos and gives feedback to each participant monthly. In addition, food diary information is also collected at the 3-month time point in order to give more dietary suggestions to the subjects. A clinical nutritionist will hold nutritional education meetings three times for the diet and AEx + LCh groups during the intervention period.

For the control and reference groups, we will keep in contact with them via phone call monthly and questionnaire to check on their physical condition and lifestyle at 3 and 6 months follow-up during the intervention.

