#### Sample size estimation

The sample size calculation (drawing on previous literature) with an estimate of how many participants will be needed for the primary outcome to be statistically, clinically and/or politically significant. For the specific primary outcome of liver fat and microbiota, based on our plot study, 34 subjects in each group would have 85% power for mean comparison between the randomized groups for the liver fat. We set the significance level at 0.05 and allowed for 10 mean comparisons with the Bonferroni correction between the groups. Taking into account multi-variable comparisons in the analysis, we increase our simple size to 50 in each group. We also taking into account the compliance and drop-out (15%), thus the total number of subjects was estimated to meet each specific aim.

In addition, typical projection-based methods used to analyze whole-genome data, such as Principal Component or Partial Least Squares Regression, do not have statistical inference methods. Thus, the corresponding methods for sample size estimation are data-driven methods involving latent variables. However, the large dimension and the time series nature of our datasets provide a good opportunity for inferring associations between different measurements. By using a systems biological approach we can develop models based on path analysis, which comprehensively integrate data for analysis. With such models we will be able to reveal the relationships between different variables.

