### Statistical methods

All data collected by questionnaires will be entered into database management software (Filemaker Pro version 10, FileMaker Inc. Santa Clara, CA, USA), double checked by independent researchers, and exported to PASW statistics version 20 (IBM Corporation, USA). If data is not normally distributed, their natural logarithms will be used for further analysis. Descriptive statistics will be used to present the background and anthropometric data at the baseline and follow-up assessments as mean and 95% confidence interval (CI) unless otherwise stated.

An intention-to-treat (ITT) analysis will be performed to compare the AEx, LCh and AEx + LCh groups to Con group. The effects of the interventions will be assessed using analysis of variance (ANCOVA) for repeated measures (treatment group × time) and baseline difference as a covariate. If the significance of the group by time interaction is p < 0.05, the effect will be localized utilizing Bonferroni for multiple comparisons. The level of statistical significance chosen for the contrasts will be p < 0.05. In addition to the ITT analysis, efficacy or active treatment analysis will be done when the compliance of the participation of the intervention is ≥60% of the whole trial and for <60% not more than 3 months continuously [ANCOVA for repeated measures (treatment group × time) and baseline difference as a covariate.] The percentage differences (0–6month) will be calculated from duration between baseline and end point measurements for each individual. The comparison of percentage changes in different groups will be performed using ANCOVA (two factor interactions: compliance/noncompliance × treatment group) controlled for the baseline value using Bonferroni for multiple comparisons. If the significance of the overall group difference is p < 0.05, then the effect will be localized by contrast to the Con group. When the 95% CI does not include zero, the difference is regarded as statistically significant at α = 0.05.

Linear Pearson’s correlation, partial correlation, Kendall Tau’s, and bivariate, logistic, and multivariate regression analysis will be used for analysing relationships. In addition, systems biology approaches will be used to develop models which integrate the different types of data and the high-throughput data measured in terms of gut microbiota composition and fecal SCFAs content, as well as LPSs and inflammation.

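### Exercise is delivered in teams of about ten, but the planned ANCOVA has no team term; if outcomes correlate within teams, standard errors for the exercise arms versus control are too small

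*Protocol article*

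**What the plan says.** Under Concomitant adherences and procedures, the article says "We will organize the participants into groups according to their time and places of residence". It expects exercising as a team to improve compliance and has an instructor with the subjects at least three times a week. It adds: "A group leader of each 10 subjects will be selected by participants to assist the instructor to ensure a high participation rate". Under Interventions, the AEx + LCh group follows the same exercise programme as AEx. Control and reference participants are contacted by monthly telephone call and by questionnaire at 3 and 6 months; no grouping is described for them.

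Under Randomization methods, individuals are allocated in 10 blocks of 20. Under Statistical methods, the three intervention arms are compared with Con by intention to treat, and "The effects of the interventions will be assessed using analysis of variance (ANCOVA) for repeated measures (treatment group × time"), with baseline as covariate. No term for team, leader or instructor appears.

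Under Sample size estimation, "34 subjects in each group would have 85% power for mean comparison between the randomized groups for the liver fat", and "We set the significance level at 0.05 and allowed for 10 mean comparisons with the Bonferroni correction between the groups". The figure is then raised to 50 per group, with 15% allowed for compliance and drop-out. Clustering is not mentioned.

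**The concern.** Individuals are randomised, but after randomisation those in the two exercise arms are treated in groups. This is a partially nested design: clusters in the exercise arms, none in control. The protocol relies on the team to change how much exercise people do. If some teams and leaders succeed better than others, adherence, and through it liver fat, will be more alike within a team than between teams. A model that treats all participants as independent then understates the variance of the exercise-arm mean.

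At stake are two of the three planned comparisons with control. Their confidence intervals would be too narrow and their P-values too small, by an amount that depends on the within-team correlation and on how teams are made up. The article gives neither.

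**Working it through.** **Inputs from the article.** Teams of about 10; 50 per arm, so 50/10 = 5 teams if teams are arm-specific; 15% loss, so 50 × 0.85 = 42.5, about 42 evaluable per arm; 85% power with 34 per group; 0.05 Bonferroni-corrected for 10 comparisons, 0.05/10 = 0.005.

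**Assumptions, not in the article.** ICC 0.01 to 0.10; two-sided tests; equal variances; evaluable team sizes 9, 9, 8, 8, 8; an unadjusted two-sample t test standing in for the planned ANCOVA. The ICC meant here is the one remaining after baseline adjustment.

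**The plan's own figure.** The article cites only a pilot study and gives no effect size or SD, so 34 per group cannot be reproduced independently. Solving backwards, d = (2.807 + 1.036) × √(2/34) = 0.93 SD by the normal approximation, or 0.96 SD with the t distribution. Without clustering, power at that difference is about 93% with 42 per arm.

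**Variance, arm-specific teams.** Σm²/Σm − 1 = (81 + 81 + 64 + 64 + 64)/42 − 1 = 354/42 − 1 = 7.43. Since only the exercise arm is clustered,

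true variance / model variance = (2 + 7.43 × ICC)/2,

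and the share by which the model understates the true variance is 1 − 1/ratio.

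**Variance, mixed teams.** If balanced, a block of 20 over four arms yields 5 AEx and 5 AEx + LCh, which is one natural team of ten. Each arm then has 4 or 5 evaluable members in each of ten teams: (2 × 25 + 8 × 16)/42 − 1 = 178/42 − 1 = 3.24, so the ratio is (2 + 3.24 × ICC)/2.

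Type I error was simulated with at least 40,000 trials per ICC:

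| ICC | Ratio, arm-specific | Understated by | Type I at 5% | Type I at 0.5% | Ratio, mixed | Type I at 5%, mixed |
|---|---|---|---|---|---|---|
| 0.01 | 1.04 | 4% | 5.3% | 0.6% | 1.02 | 5.2% |
| 0.03 | 1.11 | 10% | 6.4% | 0.8% | 1.05 | 5.5% |
| 0.05 | 1.19 | 16% | 7.0% | 0.9% | 1.08 | 5.9% |
| 0.10 | 1.37 | 27% | 9.5% | 1.6% | 1.16 | 7.0% |

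At a Bonferroni level for the three control comparisons (0.05/3 = 1.67%), arm-specific teams give about 1.9%, 2.3%, 2.8% and 4.2%. At ICC 0 every figure returns to its nominal level.

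**Sample size.** With arm-specific teams of 10, the design effect in the exercise arm is 1 + 9 × ICC. At 0.93 SD and alpha 0.005, the normal approximation needs 36 per arm for 85% power at ICC 0.01, 42 at 0.05 and 50 at 0.10. About 42 completers therefore cover an ICC up to about 0.05, before any penalty for the small number of teams.

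**The case against.** The strongest reply is that nothing shows the ICC to be material. A team that raises adherence everywhere shifts the mean without creating differences between teams. Exercise is prescribed on each person's fitness and monitored by heart rate. An instructor shared by all teams adds no between-team variance. Shared residence alone does no harm, because individuals are randomised. The inflated error rates also need a particular null: teams must move liver fat by different amounts while the average effect of exercise is zero. All of this stands, and it makes the claim conditional. It does not make zero the right value to build in, and too-narrow intervals do not depend on the null being true.

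A second reply is that teams may mix the two exercise arms. That also stands: the excess variance against control is then less than half as large. For AEx versus AEx + LCh, the planned standard error would even be slightly too large, since the true one is √(1 − ICC) times it.

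A third is that a condensed article leaves random effects and degrees of freedom to the SAP. This is fair for the technical detail. But the article names a model that takes participants as independent, and team membership has to be captured while exercise is being delivered. It may be hard to reconstruct later.

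A reader might go further and infer that the standard errors are in fact too small, or that 50 per group is too few. The article supports neither: the first needs an ICC it does not give, and the sample size has slack at the back-solved effect.

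**Conclusion.** The point holds in conditional form. The article describes team delivery in the exercise arms and fixes an analysis that ignores it. For any positive within-team correlation, the standard errors for AEx versus Con and AEx + LCh versus Con are too small. Over an assumed ICC of 0.01 to 0.10 with arm-specific teams, the true variance is 4% to 37% above the model's, which means the model understates it by 4% to 27%. At the low end of the ICC range, or with mixed teams, the effect is minor. At the upper end with arm-specific teams, it nearly doubles a nominal 5% error and roughly triples a nominal 0.5% error. These sizes rest on the assumed ICC, about five teams per arm and an unadjusted comparison. This is a worthwhile, inexpensive improvement to the plan and not a demonstrated error in any stated figure.

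**What to change.** Record each participant's exercise team, and state whether teams are arm-specific or mix AEx and AEx + LCh. The article has recruitment running to June 2014, so this can still be captured at delivery for later enrolees.

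Pre-specify a partially nested mixed model: a random team effect in the exercise arms only, shared across them if teams mix, fitted by REML with Satterthwaite or Kenward-Roger degrees of freedom. Report it next to the planned ANCOVA, at least as a sensitivity analysis. Give the estimated ICC with its imprecision, which will be large with so few teams.

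Recording costs one variable. The analysis costs power. In the most conservative version (a comparison of team means with Satterthwaite degrees of freedom) at alpha 0.005 and 0.96 SD, with 42 per arm:

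| | Unclustered | Team means, arm-specific | Team means, mixed |
|---|---|---|---|
| ICC 0 | 93% | about 81% | about 89% |
| ICC 0.05 | 92% | about 69% | about 86% |

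The unclustered 92% at ICC 0.05 is partly bought with an inflated error rate, so the two columns are not like for like. The loss is still large enough that the choice between primary and sensitivity analysis should be made, and justified, before the data are seen.
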